### 15 Prior Approvals

Describe any approvals that will be obtained prior to commencing the research. (E.g., school, external site, funding agency, laboratory, radiation safety, or biosafety approval.)

Radiation safety approval will be obtained prior to commencing the research and we will add this protocol to our current IBC disclosure # 12 -491.

### 16 Data Management and Confidentiality

Describe the data analysis plan, including procedures for statistical analysis.

Describe the steps that will be taken to secure the data during storage, use, and transmission.

- Training, authorization of access, password protection, encryption, physical controls, certificates of confidentiality, and separation of identifiers and data

Describe how data and any specimens will be handled:

- What personal identifiers will be included in that data or associated with the specimens?
- Where and how data or specimens will be stored?
- How long the data or specimens will be stored?
- Who will have access to the data or specimens?
- Who is responsible for receipt or transmission of the data or specimens?
- How will data and specimens be transported?
- If data or specimens will be banked for future use, describe where the specimens will be stored, how long they will be stored, how the specimens will be accessed, and who will have access to the specimens.
- Describe the procedures to release data or specimens, including: the process to request a release, approvals required for release, who can obtain data or specimens, and the data to be provided with specimens.

## BIOSCIENCE INSTRUCTIONS AND TEMPLATE

NUMBER

HRP-503b

DATE

3/22/2022

PAGE

11 of 13

**Specific Aim 1:** We will test the hypothesis that adolescents who complete the intervention will exhibit significantly greater short-term and long-term improvements in glucose tolerance and increases in insulin sensitivity compared to UCC. ANCOVA models will use pretest measures as a covariate and the experimental groups (i.e., intervention vs. UCC) for comparisons. Separate analyses will be conducted for 6- and 12-months. We will explore interactions between the covariate (baseline measure) and group to determine whether adolescents with lower baseline scores differentially benefit from the program. Assuming no interaction is found, we will examine the main effect of group assignment on the outcome measure after adjusting for baseline. We will also conduct repeated measures ANCOVA models to examine differences in the effect of the intervention on primary outcomes between 6- and 12-month time points.

**Specific Aim 2:** We will use the same ANCOVA models described above to examine the effects of the intervention on general and weight-specific QoL. Results will indicate whether adolescents who were randomized to the intervention report greater increases in QoL compared to adolescents randomized to UCC.

**Specific Aim 3:** We will explore the mediating effects of changes in total body composition on changes in T2D risk markers by path analysis. Each mediation model will include three variables: (1) experimental group membership represented by dummy codes, (2) a mediator measure (e.g., fat mass), and (3) an outcome measure. The model specifies direct paths from group membership to the mediator and outcome. Path coefficients and standard errors for these paths will be estimated. Effect size measures will include: (1) direct effects on outcome and (2) mediated or indirect effects on outcome. The latter will be estimated using path coefficient estimates with standard errors.

**Specific Aim 4:** To examine the cost effectiveness of the intervention, we will estimate the incremental cost-effectiveness ratio (ICER) of the intervention compared to UCC based on changes in 2-hour glucose. The cost effectiveness analyses will be conducted from the societal perspective using 2-hour glucose at 12 months, direct medical costs, and non-medical costs. Direct medical costs include: personnel, intervention materials, MD and RD visits, lab tests, and procedures. The non-medical costs will be participant time for travel, productivity loss, and commercial services for PA and nutrition. Base case and sensitivity analyses will be conducted using TreeAge software. The base case analysis model will use 6-month intervention costs and glucose tolerance at 12-months. ICERs will be calculated by dividing incremental costs by incremental effectiveness (change in 2-hour glucose). The results will indicate whether improved glucose tolerance leads to cost savings. Costs collected throughout the study will be inflated based on the published inflation rates in US dollars at the end of the study.

Confidentiality will be protected through the use of study identification numbers that will be kept separate from personal identifiers. A secure, password protected database will serve as the link between study IDs and source documents which will be kept in separate double-locked file cabinets at Arizona State University in the Southwest Interdisciplinary Research Center (SIRC) data storage in the UCENT building room 700. With the exception of the consent, contact information sheet, eligibility, clearance forms, and lab reports used in the context of the lifestyle class, all study materials will identify participants solely by the assigned code numbers. Blood specimens will be stored with ID numbers in the PI's freezer in ABC-1 rm 259-A. Members of the research team will have access to de-identified data. ID numbers will be used and de-identified data will be entered into a password protected computerized database after baseline testing and confirmation of eligibility. Data will be stored for 7 years; paper documents will be shredded and electronic files will be erased.

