### 9 Withdrawal of Participants

Describe anticipated circumstances under which participants will be withdrawn from the research without their consent. Describe procedures that will be followed when participants withdraw from the research, including partial withdrawal from procedures with continued data collection.

- Participants are free to withdraw from the study at any time. If a participant notifies a staff member that they no longer want to participate in the study, this choice will be documented in their study chart and in the database. They will be told that withdrawal will not impact any services or relationship with ASU, St. Vincent de Paul, or the YMCA. We will not be scheduled for any future study visits.
- The participants may be asked to leave the study if they:
  - Are disruptive or inappropriate during the intervention.
  - Do not attend at least 75% of the intervention sessions (54 of the 72 total).
- Participants will be contacted by study staff who will provide the justification for being withdrawn and answer any questions.

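### As written, the plan permits a completer comparison on the primary outcome, with attendance-based removal possible in the intervention arm only; this would probably favour the intervention

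*Supplement*

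**What the plan says.** The analysis text is in Section 16 (Data Management and Confidentiality). The Aim 1 hypothesis reads: "We will test the hypothesis that adolescents who complete the intervention will exhibit significantly greater short-term and long-term improvements". The comparator is usual care control (UCC). The word complete is not defined, and no matching condition is set for UCC.

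The model sentences that follow are worded differently: "ANCOVA models will use pretest measures as a covariate and the experimental groups (i.e., intervention vs. UCC) for comparisons". If there is no baseline-by-group interaction, "we will examine the main effect of group assignment on the outcome measure after adjusting for baseline". Aim 2 adopts the same models and says: "Results will indicate whether adolescents who were randomized to the intervention report greater increases in QoL compared to adolescents randomized to UCC".

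Section 9 (Withdrawal of Participants) states: "The participants may be asked to leave the study if they", and one of the grounds listed is "Do not attend at least 75% of the intervention sessions (54 of the 72 total". It adds: "Participants will be contacted by study staff who will provide the justification for being withdrawn and answer any questions". The only sentence on later visits is "We will not be scheduled for any future study visits" (garbled in the source); it stands in the bullet on participants who choose to withdraw.

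Under Section 8 (Procedures Involved), UCC youth meet an endocrinologist and a dietitian at baseline and 6 months, and are offered a shortened programme only once the study is over. The same section names the fall in 2-hour glucose as the primary outcome and says that all youth in both groups are contacted monthly so that they are available for 12-month testing.

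**The concern.** Attendance is observed after randomisation and may reflect motivation or family support. If poor attenders leave one arm and nobody leaves the other on the same ground, the remaining groups are no longer those that randomisation made comparable. A difference can then appear without any effect of the programme.

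The estimate would also answer a narrower question: the result among youth who attend well, not the result of offering the programme in place of usual care.

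Both time points of the primary outcome are exposed. So is the cost-effectiveness ratio in Aim 4, which uses 12-month 2-hour glucose. Outcomes that are not collected cannot be recovered at the analysis stage.

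**Working it through.** **The plan's own figures.** 0.75 × 72 = 54, so the attendance threshold is consistent. In Section 5, 300 screened × 40% = 120, also consistent. The protocol shown gives no power, alpha, SD, allocation ratio or expected removal rate, so the size of the problem can only be illustrated.

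**Who can trigger the rule.** Section 9 counts intervention sessions. Section 8 gives UCC youth none during the study. The rule can therefore act in the intervention arm only.

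**What happens to their outcomes.** Section 9 speaks of leaving the study, not of leaving the classes. Its template prompt asks about partial withdrawal with continued data collection, and the text under it describes none. A removed youth without a 6- or 12-month glucose drops out of the ANCOVA whichever way Aim 1 is read.

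**Illustration.** Assumptions, none of them from the documents: no true effect; 60 per arm (120 split 1:1); two-sided alpha 0.05; the lowest share q of attenders removed from the intervention arm; attendance propensity normal and correlated r with a good baseline-adjusted outcome.

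- Bias in SD of the adjusted outcome = r × φ(z_q) / (1 − q)
- SE = √[1/(60(1 − q)) + 1/60]
- Type I error = P(|Z + bias/SE| > 1.96)

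Results:

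- r = 0, any q: bias 0, type I error 5%.
- q = 10%, r = 0.2: bias = 0.2 × 0.1755/0.9 = 0.039; SE = √(1/54 + 1/60) = 0.188; ratio 0.21; type I error 5.5%.
- q = 30%, r = 0.3: bias = 0.3 × 0.3477/0.7 = 0.149; SE = √(1/42 + 1/60) = 0.201; ratio 0.74; type I error 11.5%.
- q = 40%, r = 0.4: bias = 0.4 × 0.3863/0.6 = 0.258; SE = √(1/36 + 1/60) = 0.211; ratio 1.22; type I error 23%.

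**Cross-check.** A simulated baseline-adjusted ANCOVA (8,000 runs per setting, baseline correlation 0.5 assumed) gave 0.03 SD and 5.3% at q = 10%, r = 0.2, and 0.13 SD and 11.5% at q = 30%, r = 0.3. Its SD is that of the unadjusted outcome, which accounts for the smaller bias: 0.149 × √(1 − 0.5²) = 0.129. With q = 0 the type I error was 4.8%. With r = 0 it stayed between 4.8% and 5.2% for every q.

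**The case against.** The strongest reply is that the completer wording sits in the hypothesis sentence only. The model description compares the two experimental groups and speaks of group assignment, which is as-assigned language for the primary analysis. A reader might infer from the hypothesis alone that the primary comparison is definitely not a randomised one. The documents do not settle that; they conflict. This part of the reply stands.

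Other parts also stand:

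- Removal is discretionary, so it does not follow that every poor attender leaves. The illustration's sharp cut-off is harsher than the rule requires.
- The no-further-visits sentence concerns voluntary withdrawal. One might infer that removed youth are never measured, but Section 9 is silent on them, and the monthly contact in Section 8 neither includes nor excludes them.
- Nothing in the documents links attendance to glucose or predicts how many youth would be removed, so bias towards the intervention is likely but not documented. With few removals or a weak link it is small.
- No separate analysis plan is shown, so the mere absence of a missing-data method would not be a fault on its own.

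What the reply does not remove is the text that is present: a completer-worded primary hypothesis, and a power to withdraw youth from the study that only one arm can trigger. Discretion does not help much, because case-by-case decisions by staff who know the arm open a further route for selection.

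**Conclusion.** The concern holds in this form: the plan permits a completer comparison with one-sided exclusion after randomisation, and its wording conflicts on who is analysed. The choice of population could then be made after the data are seen. Rewording Aim 1 alone would not cure it, because removed youth could still lack outcomes.

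The likely direction is towards the intervention, provided that better attenders tend to have better outcomes anyway. Under the stated assumptions the effect runs from nil (r = 0), through slight (5.5% type I error at 10% removed, r = 0.2), to serious (23% at 40% removed, r = 0.4). Confidence is high on the conflict and the one-sidedness; the size depends on assumed inputs. Because it touches the primary outcome and lost measurements cannot be recovered, it should be put right.

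**What to change.** - Reword the Aim 1 hypothesis to compare adolescents randomised to the intervention with those randomised to UCC, and name all randomised youth, as assigned, as the primary analysis set.
- Reconcile Section 9 with Sections 8 and 16 so that low attendance does not end the 6- and 12-month outcome visits unless consent for follow-up is withdrawn. This concerns outcome measurement only; whether a youth continues in the classes is for the investigators.
- State how remaining missing outcomes are handled, for example by a likelihood-based repeated-measures model or multiple imputation, with a sensitivity analysis.
- Report any completer or at-least-75%-attendance estimate as secondary, preferably as a complier-average effect, with completion defined in advance.

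The cost is wording in Sections 9 and 16 and the effort of outcome visits for low attenders. If 10% to 40% of an assumed 60 fell below the threshold, that would be 6 to 24 youth. The estimated effect may be smaller than among completers.

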Our transdisciplinary team of researchers, practitioners, and community partners has collaborated for the past 7-years to effectively address diabetes prevention challenges through the development, testing, refinement, and expansion of a culturally-grounded lifestyle intervention for obese Latino youth with prediabetes, which if efficacious, could be taken to scale. The overall approach applies an adapted Ecodevelopmental framework to leverage community, family, peer, and individual-level influences during the critical transition period of adolescence when changes in health behaviors and health outcomes are linked to future health trajectories. The intervention draws upon Social Cognitive Theory and employs key behavioral modification strategies from the DPP to enhance self-efficacy and foster social support for making healthy behavior changes. *Promotores* (community health workers) deliver nutrition education to families to facilitate dietary changes while group exercise classes for youth are led by YMCA staff to increase physical activity levels. Feasibility and initial efficacy for improving glucose tolerance and increasing insulin sensitivity was established through a pilot study. The pilot intervention also led to significant improvements in QoL, eating behaviors, fitness, and multiple cardiovascular disease risk factors without weight loss. We are currently conducting an RCT that expands upon the pilot to rigorously evaluate intervention effects in obese Latino adolescents. To date, we have enrolled 160 obese youth and the rate of prediabetes in this community sample is ~15%. Preliminary analyses on prediabetic youth show robust and sustained improvements on targeted outcomes including glucose tolerance, insulin sensitivity, and QoL. For ethical reasons, we do not randomize prediabetic youth to the control condition in that study. We now propose to build upon these compelling preliminary findings and further refine our culturally-grounded lifestyle intervention to test the efficacy, as compared to usual care, for improving health and QoL by **preventing T2D in obese Latino adolescents with prediabetes**.

**Specific Aim 1:** Test the short-term (6-month) and long-term (12-month) efficacy of this culturally-grounded, community-based lifestyle intervention as compared with a usual care control group for improving glucose tolerance and increasing insulin sensitivity in 120 obese Latino adolescents age 12-16 with prediabetes.

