### 5 Number of Participants

Indicate the total number of participants to be recruited and enrolled

- Provide a rationale for the proposed enrollment number
- What percentage of screened individuals will likely qualify for the study?

**We will screen ~300 obese Latino youth for prediabetes and anticipate that 120 will meet eligibility into the trial. These estimates are based on rates of elevated 2-hour glucose in our current study (~40% exhibit 2-hour glucose  $\geq 120$  mg/dl).**

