## BIOSCIENCE INSTRUCTIONS AND TEMPLATE

| NUMBER   | DATE      | PAGE    |
|----------|-----------|---------|
| HRP-503b | 3/22/2022 | 7 of 13 |

**Physical Activity, Fitness and Nutrition Assessment:** PA will be measured using the 3 Day PA Recall, (3DPAR), an interviewer-administered recall instrument that measures the type of PA performed during the past 3 days (e.g. Tues, Mon, Sun). The 3DPAR allows for assessment of time spent in sedentary behaviors and types of activity that can be useful to identify differences in PA patterns between adolescents. Cardiorespiratory fitness ( $Vo_{2peak}$ ) will be estimated by a submaximal exercise test developed and validated for obese youth. Participants walk on a treadmill at a self-selected speed at 0% grade for 4 minutes. The grade is then increased to 5% while speed is maintained for 4 more minutes. Heart rate is recorded at the end of the 8 minutes and entered into the prediction equation. Dietary intake will be measured using the 2007 Block Food Screener for Ages 2-17. This 41-item screener assesses foods eaten during the previous week and was designed to identify dietary intake by food group. National dietary surveys were used to inform the food selections to query, as well as to identify appropriate portion sizes and nutrient composition. This screener includes items commonly consumed by Latino youth and has been used to assess changes in dietary factors in Latino youth.

**Intervention (Nutrition Education):** The intervention curriculum was developed through an inductive, collaborative process with our community partners and subsequently refined through a series of increasingly rigorous projects starting with a clinical demonstration project, a pilot study, and our ongoing RCT. The curriculum is informed by Social Cognitive Theory and applies key behavioral change strategies from the adult DPP and other successful lifestyle interventions such as goal-setting, fostering social support, and enhancing self-efficacy to facilitate health behavior change. The education curriculum is tailored for the unique psychosocial and developmental characteristics of obese adolescents and grounded in the Latino culture. Sessions (N=20) are delivered at the YMCA to groups of 8-10 families (parent/guardian participation is a requirement) by bilingual/bicultural community health educators from the Family Diabetes Program at St. Vincent de Paul Medical and Dental Clinic.

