Children are presented with the results of their glucose tolerance test in the first class as a way to frame the discussion around diabetes and health. Each session begins with a low fat, high fiber snack and recipe (role modeling), acknowledgment and reinforcement of healthy behavior changes and progress towards individual goals (emotional and instrumental support), problem-solving challenges, and an outline of the session's goals. Children are incentivized through a point system for attendance, completing out of class 'assignments' such as helping to prepare a healthy meal for the family (enacting behaviors), participating in group discussions, and making progress towards their individual health goals. Parents and children work with other families during classes and are encouraged to do so outside of class in order to build a support network that extends beyond the program. Classes are delivered using a tiered approach where the first 16-sessions are delivered weekly while the last 4 session are spread over 8 weeks (total intervention period is 6-months). We have found that this delivery approach builds resiliency within families as they become less reliant on the health educators and more independent in achieving their health and behavior goals. Following the intervention period, children will return for post-intervention testing.

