**Intervention (Physical Activity):** The PA intervention includes structured and unstructured components. The structured PA curriculum is led by YMCA instructors and delivered 2 days/week to groups of 8-10 youth (both boys and girls) for 60-minutes each. Classes include aerobic and resistance exercises delivered in a progressive manner with the first 2-4 weeks focusing on motor skill acquisition, exercise confidence, developing a fitness base, and building camaraderie among participants. Aerobic exercises include group activity classes (e.g. spinning and cardio kick-boxing) with the goal of maintaining heart rates > 150 BPM. Real-time heart rate monitoring and rate of perceived exertion are used to monitor and document exercise intensity throughout the program. This exercise intensity was selected for the established effects on improving metabolic health in obese youth. Resistance exercise includes circuit training using age and size appropriate equipment and is incorporated because our previous studies suggest this form of exercise is both enjoyable and metabolically beneficial for obese youth. In addition to structured PA classes, youth are 'prescribed' an additional day of unstructured PA of at least 60-minutes with a family member or peer in the program. This allows for flexibility in pursuing preferred activities that can be done at the YMCA or elsewhere in the community in order to promote social support, role modeling, bonding among youth and families, and facilitate sustainability.

**Booster Sessions:** Three booster sessions (months 7, 8, and 9) following the completion of the intensive lifestyle period will be held to support the maintenance of healthy lifestyle behaviors, address any challenges encountered, and promote successes achieved. Post-intervention clinical measures will be returned to participants at the first session and changes in health status will be discussed in the context of maintaining healthy lifestyle behaviors.

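### The ANCOVA ignores that intervention youth are treated in groups of 8-10; if outcomes correlate within groups, its standard errors are too small and its tests anti-conservative

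*Supplement*

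**What the plan says.** Section 16 (Specific Aim 1) gives the model: "ANCOVA models will use pretest measures as a covariate and the experimental groups (i.e., intervention vs. UCC) for comparisons". It is fitted separately at 6 and 12 months, with a repeated measures ANCOVA to compare the two time points. Specific Aim 2 uses the same models for quality of life. Section 16 mentions no delivery group, clustering, random effect or robust standard error.

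Section 8 describes group treatment in one arm. Nutrition sessions "are delivered at the YMCA to groups of 8-10 families". Structured exercise is "delivered 2 days/week to groups of 8-10 youth (both boys and girls) for 60-minutes each". Mutual influence is intended: "Parents and children work with other families during classes and are encouraged to do so outside of class". Section 8 also describes UCC, where participants meet an endocrinologist and a dietitian at baseline and 6 months. No group delivery is described for them until the abridged programme offered after the study.

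Section 2 (Specific Aim 1) sets the sample "in 120 obese Latino adolescents age 12-16 with prediabetes".

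**The concern.** Two youths in the same delivery group share sessions, peers and a support network that the programme deliberately builds. If that mechanism works, their outcomes may be more alike than those of two youths in different groups. A model with only baseline and arm counts a group of 8-10 as 8-10 independent observations. Positive correlation then makes the reported standard error too small, the confidence interval too narrow and the p-value too low. The error favours a false positive, and it reaches the primary outcome (2-hour glucose), insulin sensitivity and quality of life. With few groups, one unusually good or poor group can also carry much of the result.

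**Working it through.** **Inputs from the documents.** Total sample 120 (Sections 2 and 5). Group size m = 8 to 10 (Section 8). Primary outcome 2-hour glucose, continuous (Section 8).

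**Inputs assumed because the documents do not give them.** Allocation 1:1, so 60 per arm (2:1 also checked). Two-sided 5% test. ICC from 0 to 0.10. Equal total variance in both arms.

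**Step 1: the plan's own figure.** Section 5 expects 120 eligible from about 300 screened at about 40%: 300 x 0.40 = 120. This reproduces, but it is a screening yield and says nothing about precision or error rates.

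**Step 2: number of groups.** 60/10 = 6 and 60/8 = 7.5, so about 6 to 8 groups.

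**Step 3: formulas.** With clustering in one arm only and unit total variance:

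- Naive variance = 1/60 + 1/60
- True variance = [1 + (m-1) x ICC]/60 + 1/60
- Ratio = {[1 + (m-1) x ICC] + 1}/2
- True SE / naive SE = square root of the ratio
- Actual type I error = 2 x [1 - Phi(1.96 / SE ratio)]

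**Step 4: worked case, ICC 0.05.**

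- m = 8: design effect in the arm 1 + 7 x 0.05 = 1.35; variance ratio (1.35 + 1)/2 = 1.175; SE ratio 1.084; 1.96/1.084 = 1.808; type I error 7.1%.
- m = 10: design effect 1.45; variance ratio 1.225; SE ratio 1.107; 1.96/1.107 = 1.771; type I error 7.7%.
- Effective size of the intervention arm: 60/1.35 = 44 to 60/1.45 = 41.

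**Step 5: over the range (60/60, m = 8 to 10).** The simulation ran the planned ANCOVA 20,000 times per setting, with an assumed baseline-outcome correlation of 0.5.

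| ICC | True SE / naive SE | Type I error, formula | Type I error, simulated |
|---|---|---|---|
| 0 | 1.00 | 5.0% | 5.0-5.1% |
| 0.01 | 1.02 | 5.4-5.5% | 5.2-5.4% |
| 0.02 | 1.03-1.04 | 5.8-6.1% | 5.6-5.8% |
| 0.05 | 1.08-1.11 | 7.1-7.7% | 7.1-7.6% |
| 0.10 | 1.16-1.20 | 9.2-10.4% | 8.7-10.4% |

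The ratio column says how much larger the true SE is than the naive one. Put the other way (1 - 1/ratio), the naive SE is about 8-10% too small at ICC 0.05 and 14-17% too small at 0.10.

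**Step 6: 2:1 allocation (80/40).** Formula type I error is 6.4-6.8% at ICC 0.05 and 7.8-8.6% at 0.10, so the inflation shrinks but remains.

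**Step 7: can the group variance be estimated?** Take 7 groups of 60/7 = 8.57. The one-way ANOVA estimate of the between-group variance is zero or negative with probability P(F < 1/[1 + m x ICC/(1-ICC)]), where F has 6 and 53 degrees of freedom. At ICC 0.05 the threshold is 1/1.451 = 0.689 and the probability about 34%. At ICC 0.02 it is 1/1.175 = 0.851 and about 46%. A zero estimate will be common, so the remedy has to provide for it.

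**The case against.** The strongest reply is that nothing in the documents shows a positive ICC. At ICC 0 the planned test is nominal, and at 0.01-0.02 the excess is about 0.4 to 1 point. A reader might infer that type I error certainly exceeds 5%. The documents do not support that, since they state no ICC, significance level or allocation ratio. Nor would group delivery by itself create correlation if the programme changed nothing for anyone. The figures describe a zero average effect with real variation between groups.

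A reader might also infer randomisation of intact groups, fixed membership of one class for all sessions, or strictly individual UCC visits. Section 8 supports none of these. Youth are randomised and then grouped. Nutrition and exercise group sizes are given separately, with nothing on whether membership is the same or fixed. UCC visits are described without the word individual. Staff are not assigned to groups either; if the same staff teach every group, they add little between-group variation. The ICC may also differ between 6 months and 12 months, because the intensive period ends at 6 months and only three boosters follow.

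Finally, this is a short institutional protocol template, no separate SAP is shown, and fine detail of a covariance model is often left to one. That limits the severity. It does not remove the point: Section 16 is not silent but names a model, and that model has no place for the group delivery that Section 8 describes.

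**Conclusion.** The point holds as a conditional statement. The design is partially nested, with grouping in the intervention arm only, and the stated ANCOVA for Aims 1 and 2 treats all youth as independent. Any positive within-group correlation makes it anti-conservative. The size depends on assumptions: under 1:1 allocation and a two-sided 5% test, it runs from nothing at ICC 0 to roughly a doubling of the nominal error at ICC 0.10, with about 7-8% at ICC 0.05. The protocol's reliance on peer support makes an ICC of exactly zero an awkward assumption, but it does not fix a value. Severity: should-fix.

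**What to change.** Record the delivery group of every intervention youth, separately for nutrition and exercise if the memberships differ. In Section 16, replace the ANCOVA for Aims 1 and 2 with a baseline-adjusted, partially nested mixed model:

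- a random group effect in the intervention arm only;
- separate residual variances by arm;
- Satterthwaite or Kenward-Roger degrees of freedom.

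Keep the group term whatever its p-value. State in advance what happens if the group variance is estimated as zero: for example, allow a negative within-group covariance, or report a sensitivity analysis over a range of fixed ICCs. Report the ICC with its interval at 6 and at 12 months. Carry the group term into the repeated measures model as well.

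The cost is one recorded variable and revised analysis wording, with no change to how the intervention is delivered. The price is slightly wider intervals, fewer degrees of freedom and an imprecise ICC from about 6 to 8 groups. Group membership may be hard to reconstruct later if it is not recorded.
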